**Methods:**

This protocol describes a prospective single-arm interventional study enrolling patients with symptomatic and radiographically confirmed CMC-1 OA. All eligible participants will undergo US-guided intra-articular injection with LWPs. The primary endpoint will be the change in pain during activity after 3 months. Secondary outcomes will include pain at rest, hand disability, grip and key pinch strength, rescue analgesic consumption, patient-reported improvement, ultrasonographic findings, treatment-related adverse events, and pain during activity and at rest after 1, 3 and 6 months.

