## Eligibility criteria

Eligibility will be established on the basis of clinical, radiographic, and procedural criteria. Table 1 summarizes the proposed inclusion and exclusion criteria.

**Table 1 T1:** Proposed eligibility criteria for enrollment.

Inclusion criteria	Exclusion criteria
Age ≥40 years	Prior thumb base surgery on the affected side
Symptomatic CMC-1 joint OA for over 3 months (joint pain, joint stiffness, decreased mobility, deformity, instability, functional impairment)	Intra-articular injection in the target joint within the previous 3 months
Radiographic confirmation of CMC-1 joint OA using the Eaton-Littler classification	The Eaton-Littler classification grade IV
Pain at the thumb base for at least 3 months	Inflammatory arthritis or crystal arthropathies with treatment changes during the previous 3 months or planned treatment changes during follow-up
Insufficient response to standard conservative treatment	Active local or systemic infection
Average pain intensity ≥4/10 during hand use in the week before enrollment as assessed by NRS for pain	Known hypersensitivity to collagen-derived products or study excipients
Ability to provide written informed consent	Coagulation disorder or anticoagulation judged_incompatible with the procedure
	Pregnancy or breastfeeding
	Neurological or musculoskeletal conditions that could interfere with outcome assessment: carpal tunnel syndrome, ulnar neuropathy, cervical radiculopathy, peripheral neuropathy, multiple sclerosis, stroke, motor neuron disease and Parkinson disease, ligament injuries (e.g., Skier's Thumb) and Dupuytren disease
	History of severe hand and thumb trauma
	Impossibility of safe US-guided injection as assessed by the investigator
	US visible extravasation of the injectate LWPs outside the joint space during the procedure

CMC-1, first carpometacarpal joint; OA, osteoarthritis; NRS, numerical rating scale; US, ultrasound.

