## US-guided injection procedure

All procedures will be performed by an experienced physician trained in musculoskeletal US-guided interventions. The injection will be performed with hand placed on a solid surface with the palm facing upward. A high-frequency linear transducer will be used to identify the CMC-1 joint and to guide needle placement in real time in-plane approach to ensure more precise injection. A single US-guided intra-articular injection of 1 mL of LWPs will be administered into the CMC-1 joint through a 23-gauge needle. Correct intra-articular delivery will be confirmed using US guidance. This approach is methodologically justified in this joint because thumb CMC injections are technically demanding and have lower landmark-based accuracy than several other common hand injections (26).

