## Statistical analysis

Analyses will be performed according to a predefined statistical analysis plan. Because the protocol is currently single-arm and non-randomized, the primary analytical population should include all enrolled participants who receive the injection and provide at least one post-baseline assessment. A per-protocol analysis may be performed as a sensitivity analysis.

Descriptive statistics will summarize baseline demographic, clinical, radiographic, and ultrasonographic characteristics. The primary endpoint—change in pain during activity from baseline to 3 months—may be analyzed with a paired-samples approach or, preferably, with a mixed-effects repeated-measures model including time as a fixed effect and participant as a random effect. Continuous secondary outcomes may be examined with similar longitudinal models, whereas categorical responder analyses may be reported descriptively or explored with appropriate regression methods if sample size permits. Missing data should be handled according to a prespecified strategy consistent with the amount and mechanism of missingness. If sample size allows, exploratory analyses may be performed to assess whether baseline clinical, radiographic, or US features are associated with clinical response (27).

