## Safety monitoring

Safety surveillance will include systematic recording of local and systemic adverse events throughout the study. Particular attention will be paid to post-injection pain flare, swelling, bruising, local inflammatory reaction, hypersensitivity, infection, neurovascular injury, and clinically meaningful worsening of symptoms. Serious adverse events will be reported according to local institutional and regulatory requirements.

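### Table 1 excludes patients for leakage that can be seen only once injection has begun, which conflicts with the primary population of all enrolled participants injected

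*Protocol article*

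**What the plan says.** Under Eligibility criteria, the article announces that "Eligibility will be established on the basis of clinical, radiographic, and procedural criteria". Table 1 is captioned "Proposed eligibility criteria for enrollment", and the last row of its exclusion column reads "US visible extravasation of the injectate LWPs outside the joint space during the procedure".

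Four other places bear on the same patients:

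- **Abstract, Methods:** "All eligible participants will undergo US-guided intra-articular injection with LWPs". Eligibility is settled first and injection follows.
- **US-guided injection procedure:** "A single US-guided intra-articular injection of 1 mL of LWPs will be administered into the CMC-1 joint through a 23-gauge needle". Delivery into the joint is checked by ultrasound at that time.
- **Statistical analysis:** "the primary analytical population should include all enrolled participants who receive the injection and provide at least one post-baseline assessment". A per-protocol analysis is allowed as a sensitivity analysis.
- **Safety monitoring:** "Safety surveillance will include systematic recording of local and systemic adverse events throughout the study".

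The article gives no extravasation rate, no expected outcome for patients in whom it occurs, and no final sample size.

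**The concern.** An exclusion criterion should be decidable before treatment. This one depends on how the treatment went, so it selects on a post-treatment event. The row just above it, on whether a guided injection can be done safely, can be judged beforehand; this one cannot.

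The design makes the selection matter. With one arm, the before-after change in activity pain is the whole efficacy result, and no control group undergoes the same selection. If patients with visible leakage are removed, the trial estimates the change after technically clean injections. The Conclusion, however, describes a study of guided injection in patients with symptomatic disease. A clinician choosing the procedure cannot know in advance which injections will be clean.

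Safety is a co-objective. The events that Safety monitoring singles out include swelling, local inflammatory reaction and neurovascular injury, and for these a patient with product outside the joint is of obvious interest.

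**Working it through.** The article states no figure on this point, so there is none to reproduce. The check is a reading of the sections together, followed by an illustration on assumed inputs.

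**Step 1. When can the criterion be met?** Injectate cannot leave the joint space before injection starts. By then the patient has consented (Ethics and data management puts consent before any study-specific procedure), has completed the baseline measures (Intervention) and has received at least part of the 1 mL. Anyone who meets the row is therefore an exposed patient.

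**Step 2. Is such a patient in the primary population?** There are two readings.

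| Reading | Table 1 | Statistical analysis | Result |
|---|---|---|---|
| A: the row decides enrollment | Not enrolled | Requires enrollment | Injected patient leaves the primary population |
| B: enrollment precedes injection | Excluded | Enrolled and injected, so kept | The two sections give opposite answers |

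The wording in Statistical analysis (enrolled, then injected) and the timing of baseline measures in Intervention both fit reading B. The caption of Table 1 fits reading A. The article does not settle which applies, so centres could differ. The pre-study calibration exercise would not prevent this, because it covers scoring of inflammatory and structural findings and not leakage.

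Under reading B, the patient must still provide at least one post-baseline assessment. A centre that treats the row as ending participation would collect none, and the patient would be lost from the primary population after all.

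**Step 3. Efficacy illustration (all inputs assumed).** Let f be the share of injected patients removed for leakage, m1 the mean NRS reduction in those kept and m2 the mean in those removed.

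- All-injected mean = (1 − f) × m1 + f × m2
- Overstatement = m1 − all-injected mean = f × (m1 − m2)

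Take m1 = 2.0, which is the clinically significant reduction named under Outcome measures and is used here only to set the scale.

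| f | m2 = 2.0 | m2 = 1.0 | m2 = 0 |
|---|---|---|---|
| 5% | 0 | 0.05 | 0.10 |
| 10% | 0 | 0.10 | 0.20 |
| 20% | 0 | 0.20 | 0.40 |
| 30% | 0 | 0.30 | 0.60 |

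Entries are the overstatement in NRS points. In the worst cell the all-injected mean is 0.7 × 2.0 + 0.3 × 0 = 1.4, against 2.0 reported. If leakage does not affect the outcome, the overstatement is zero at any rate.

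**Step 4. Safety illustration (all inputs assumed).** This applies only if these patients' events were not counted, which the article does not say. With a local event rate of 10% in those kept, the all-injected rate is (1 − f) × 10% + f × (rate in those removed).

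- Rate of 10% in those removed: 10% throughout, so no understatement.
- Rate of 20%: 10.5%, 11%, 12% and 13% for f = 5%, 10%, 20% and 30%.
- Rate of 40%: 11.5%, 13%, 16% and 19%.

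In every case 10% would be reported.

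**The case against.** The strongest reply is that Statistical analysis already keeps everyone enrolled and injected. If enrollment precedes injection, leaking patients stay in and no bias arises. That reading is fair, and it is why loss from the efficacy analysis is conditional here. It does not remove the problem, because Table 1 still excludes the same patients.

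A reader might go further and infer that these patients leave follow-up, that their adverse events are discarded and that the technical failure rate will go unreported. The article says none of this. Safety monitoring names no exception, and a formal definition of the safety set may well stand in the full protocol or analysis plan. What remains is narrower: recording is tied to the study, Table 1 takes these patients out of it, and nothing printed assures their follow-up.

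A reader might also infer that leakage will be common, because the article says that "thumb CMC injections are technically demanding". That remark goes on to compare landmark-based accuracy and is there to justify ultrasound guidance. The Introduction expects guidance to reduce extra-articular injection. The remark therefore says nothing about the leakage rate under guidance, in either direction.

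Nor do the illustrative figures show that a conclusion would change. With assumed reductions of 2.5 points after clean delivery and 1.0 after leakage, 30% leakage gives 0.7 × 2.5 + 0.3 × 1.0 = 2.05, still beyond 2 points.

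Finally, the sponsor may want the effect of true intra-articular delivery, and the reference to procedural criteria suggests that the row is deliberate. That is a legitimate question, but it belongs to the per-protocol analysis, which the article already allows. The Discussion also concedes limits on causal inference and external validity, though for other reasons: no control arm, no blinding and an exploratory sample size.

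**Conclusion.** The point holds as an error in the text as written. A finding that can arise only in an exposed patient is listed as a criterion for entry, and it conflicts with both the order of events in the Abstract and the primary population in Statistical analysis. If the row is applied, the primary single-arm estimate is conditional on clean delivery.

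The size is unknown. On the assumed ranges (5% to 30% leakage, 0 to 2 points less improvement after leakage) the overstatement runs from 0 to 0.6 NRS points, against the 2 points that the article calls clinically significant. Zero is a possible value. Loss of safety data is a risk that the text leaves open and not something that it states. The case for correction rests on the conflict between sections and does not depend on these figures.

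**What to change.** Reconcile Table 1 with Statistical analysis before recruitment starts, because follow-up that was not collected cannot be recovered later.

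1. Remove the extravasation row from the exclusion criteria.
2. Record extravasation at the injection on the case report form, as a procedural event.
3. State that every injected participant stays in the scheduled 1-, 3- and 6-month follow-up and in the safety population, and in the primary population under the existing rule of at least one post-baseline assessment.
4. Report the extravasation rate.
5. Restrict to participants without visible extravasation only in the per-protocol sensitivity analysis.

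The cost is one table row, one form item and a sentence or two of text, with no additional patients. The mean pain change and adverse-event rate may look slightly less favourable, but they will then describe everyone who received the injection and was assessed.

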## Intervention

Since this is a multicenter study, to maximize reproducibility, the protocol will provide a detailed description of patient positioning, skin antisepsis, US transducer orientation, needle caliber, approach to the joint, injected volume, and post-procedural recommendations. Moreover, an US calibration exercise will be performed by the sonographers of each center involved in the study. The exercise will be based on a shared database of representative US images. Each sonographer will be asked to score US images in terms of inflammatory and structural findings using semiquantitative scales (0–3) according to the OMERACT hand OA US definitions and semiquantitative scoring system, thereby improving inter-reader standardization before recruitment (24, 25).

Before enrollment, participants will complete visual analog scale (VAS) for pain at rest and during activity, and the Duruöz Hand Index (DHI) and Quick Disabilities of the Arm, Shoulder and Hand (QuickDASH). Grip strength and key pinch strength will be measured with calibrated dynamometer and pinch gauge. To improve comparability across visits and centers, the same device model should be used within each center throughout follow-up and the device characteristics should be recorded a priori.

Baseline US assessment will include the detection and semiquantitative scoring of synovial hypertrophy/effusion, power Doppler signal, and osteophytes, assessed with a high-resolution probe (B-mode frequency >15 MHz; pulse repetition frequency <1.0 kHz) using previously described and validated scanning protocols for hand OA (25).

## US-guided injection procedure

All procedures will be performed by an experienced physician trained in musculoskeletal US-guided interventions. The injection will be performed with hand placed on a solid surface with the palm facing upward. A high-frequency linear transducer will be used to identify the CMC-1 joint and to guide needle placement in real time in-plane approach to ensure more precise injection. A single US-guided intra-articular injection of 1 mL of LWPs will be administered into the CMC-1 joint through a 23-gauge needle. Correct intra-articular delivery will be confirmed using US guidance. This approach is methodologically justified in this joint because thumb CMC injections are technically demanding and have lower landmark-based accuracy than several other common hand injections (26).

## Outcome measures

The primary efficacy endpoint will be the change in pain intensity during activity, measured on a 0–10 NRS (numerical rating scale), from baseline to 3 months. A reduction of 2 points on a 10-point numerical scale is considered a clinically significant improvement in the musculoskeletal setting. Secondary endpoints will include pain at rest, DHI and QuickDASH scores, grip and key pinch strength, rescue medication use, patient global assessment, ultrasonographic findings, and adverse events. This choice is consistent with hand OA trial recommendations, which emphasize pain, physical function, patient global assessment, and—for longer studies—imaging outcomes (27, 28). Table 2 provides a summary of the assessment schedule.

**Table 2 T2:** Proposed schedule of interventions and follow-up assessments.

Assessment	Baseline	1 Month	3 Months	6 Months
Eligibility and consent	X			
NRS for pain at rest and during activity	X	X	X	X
DHI and QuickDASH	X	X	X	X
Grip and key pinch strength	X	X	X	X
US assessment	X		X	X
Injection procedure	X			
Rescue medication review		X	X	X
Adverse events		X	X	X
Patient global assessment/satisfaction		X	X	X

NRS, numerical rating scale; DHI, Duruoz Hand Index; QuickDASH, shortened Disability of Arm, Shoulder and Hand Questionnaire; US, ultrasound.

## Concomitant treatment

Stable non-pharmacological treatment, including orthoses and prescribed hand exercises, may be continued provided that these measures are documented and remain substantially unchanged during the main assessment phase. Rescue analgesia with acetaminophen/paracetamol and/or non-steroidal anti-inflammatory drugs may be allowed and recorded in patient diaries. Moreover, to minimize confounding effects, concomitant treatments will be kept stable throughout the study period whenever possible and any changes will be carefully recorded and considered in the analysis. The use of additional injections or surgical procedures targeting the study joint during follow-up should be treated as treatment failure or major protocol deviation.

## Sample size

Because the present protocol describes a single-arm prospective study, the sample size should be based on feasibility and precision of estimation rather than on a between-group superiority hypothesis. The current between-group calculation is therefore not methodologically aligned with the revised design. The final sample size should be determined with dedicated biostatistical support once the primary outcome metric, its expected variability, and the target precision or clinically important change have been definitively specified (25).

## Statistical analysis

Analyses will be performed according to a predefined statistical analysis plan. Because the protocol is currently single-arm and non-randomized, the primary analytical population should include all enrolled participants who receive the injection and provide at least one post-baseline assessment. A per-protocol analysis may be performed as a sensitivity analysis.

Descriptive statistics will summarize baseline demographic, clinical, radiographic, and ultrasonographic characteristics. The primary endpoint—change in pain during activity from baseline to 3 months—may be analyzed with a paired-samples approach or, preferably, with a mixed-effects repeated-measures model including time as a fixed effect and participant as a random effect. Continuous secondary outcomes may be examined with similar longitudinal models, whereas categorical responder analyses may be reported descriptively or explored with appropriate regression methods if sample size permits. Missing data should be handled according to a prespecified strategy consistent with the amount and mechanism of missingness. If sample size allows, exploratory analyses may be performed to assess whether baseline clinical, radiographic, or US features are associated with clinical response (27).

## Safety monitoring

Safety surveillance will include systematic recording of local and systemic adverse events throughout the study. Particular attention will be paid to post-injection pain flare, swelling, bruising, local inflammatory reaction, hypersensitivity, infection, neurovascular injury, and clinically meaningful worsening of symptoms. Serious adverse events will be reported according to local institutional and regulatory requirements.

## Ethics and data management

The study will be conducted in accordance with the Declaration of Helsinki, Good Clinical Practice principles, and applicable national regulations. Written informed consent will be obtained from all patients before any study-specific procedure. Ethics committee or institutional review board approval will be secured before the start of recruitment. Study data will be collected through standardized case report forms and stored in a secure database with controlled access.

## Expected results and clinical impact

The proposed intervention may provide clinically relevant pain improvement, better pinch and grip-related function, measurable changes in patient-reported hand disability and intra-articular power Doppler signal. These domains are particularly relevant in CMC-1 OA because disease burden often becomes evident in routine activities rather than in isolated pain scores alone. In addition, the study may help identify baseline clinical, US, and/or radiographic findings associated with better outcomes after LWPs injection.

If the intervention demonstrates both efficacy and safety, it could expand the range of minimally invasive options available to patients with persistent symptoms who are not yet candidates for surgery or who wish to postpone operative treatment. The results obtained in our cohort of patients injected with LWPs will be interpreted in the context of previously published studies, such as RHIZ'AR by Cormier et al. (9, 10).

## Discussion

Thumb base OA remains a frequent therapeutic challenge because symptoms may be substantial regardless of radiographic severity, and because patients often seek improvement in dexterity and pinch performance in addition to pain relief. In this context, a targeted injection strategy supported by biological plausibility and precise US guidance warrants formal clinical evaluation.

The present protocol has several strengths. First, it focuses on a clinically relevant and anatomically specific joint that is often underrepresented in larger OA trials. Second, the use of US guidance and a pre-study sonographer calibration procedure improve procedural consistency and internal validity. Third, the protocol incorporates both symptom-based and function-based outcomes together with objective strength measures and structured safety monitoring. Fourth, the use of disease-relevant assessment scales specifically designed for hand OA improves comparability with analogous studies and with current methodological recommendations (27, 28). Fifth, the multicentric and prospective nature of the study improve external validity and the generalizability of the findings.

Potential limitations include the absence of a control arm, the lack of blinding, and the exploratory sample size, all of which may limit causal inference and external validity. Moreover, a 6-month follow-up may be adequate for symptomatic assessment, but remains insufficient to evaluate structural disease modification. If the investigators intend to make formal comparative claims against other injective strategies, a randomized controlled design would be required. Accordingly, the present protocol should be interpreted as a prospective interventional study aimed primarily at generating structured efficacy and safety data and refining the design of future controlled trials. This design is methodologically more consistent with the current protocol rather than a parallel-group randomized one, which would require a prespecified comparator arm, allocation procedure, and blinding strategy (27).

